### Inclusion and exclusion criteria for participants

#### Inclusion parameters

Children aged 812years and their families from a low SES.Enrollment in a CCC.Informed consent signed by parents/legal representatives.

#### Exclusion parameters

Children or parents/legal representative showing psychological or physical disadvantages that make it impossible to implement the assessment protocol and project activities.

### Sample size calculation

We estimate that it will be necessary to include 270 children and their parents, both in the intervention and control groups, per edition of the FIVALIN project. We expect a statistically significant decrease in body mass index (BMI) z-score of 0.15 in the intervention group, in comparison to the control group. From the PRE to POST evaluations, for each of the three editions. Previous community intervention [35] that aimed to prevent childhood obesity through the promotion of healthy lifestyles, and were carried out in the same geographical context and among children of the same ages. They showed a mean zBMI reduction of 0.10. The FIVALIN project is a more intense intervention and, for this reason, we expect a higher zBMI reduction.

We assume a 0.05 alpha risk, a 0.2 beta risk in a bilateral contrast, and 20% loss to follow-up. We expect to recruit significantly less families with 2 children in the age range of 8 to 12years, than families with one child. Therefore, we performed a simplified approximation of the sample size by counting only for one outcome (zBMI of one child). The sample size was calculated using the online sample size and power calculator GRANMO (IMIM-Spain).

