### Subjects

The study will involve low SES children aged 812years and their families from 60 Community Child Centers (CCC) in the metropolitan area of Barcelona. A CCC is a childcare center that promotes the education of children from low income families by providing them academic support and emotional education after school. A total of 810 children and 600 parents will be included in the intervention groups, and likewise for the control groups. These population samples will be distributed among three consecutive editions of the FIVALIN project (20192020, 20202021, and 20212022), and will include at least one adult and one child per low-income family. A total of 30 CCC (15 in the intervention group and 15 as controls) will be involved per edition. CCC from control group will be invited to be part of intervention group on the subsequent edition, and15 new CCC will be recruited in the control groups of the second and third editions. In total, after the three edition, 60 CCC will be enrolled in the project (see Table1). It is not expected that CCC participating in the intervention group during first or second edition will continue providing the intervention in subsequent editions. 18 socioeconomic vulnerable children (8- to 12-year-old) and their families will participate per CCC. Therefore, considering the intervention and control groups, we expect a total participation of 540 children and 400 adults per edition. Participants will be recruited by CCC, by inviting families that are already participating in their activities. They receive communicative material (flyers and leaflets) to introduce the project and motivate them to participate. For convenience, recruitment and allocation will be conducted by Gasol Foundation (GF), considering the characteristics of the CCC: activities, number of educators, parents involvement, etc.

**Table 1 Tab1:** Number of CCC per FIVALIN edition

CCC from the	1st edition	2nd edition	3rd edition
Intervention group	1 to 15 CCC *(new)*	CCC from the control group of the 1 edition 16 to 30 CCC	CCC from the control group of the 2 edition 31 to 45 CCC
Control group	16 to 30 CCC *(new)*	31 to 45 CCC *(new)*	46 to 60 CCC *(new)*

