### Statistics

We will analyze the pooled data from the three timely different editions with a 10-month intervention each. Data clean-up will be performed to minimize errors. To compare groups, we will use the Student-t test for continuous variables and chi-square test for categorical variables. Allocation to the intervention group will be performed at the CCC level (clusters) by convenience. Therefore, generalized estimating equation (GEE) models will be fitted to assess intervention effect on BMI z-score and other secondary outcomes at individual level. To assess the outcome at family level, we will apply mixed models.

Due to the small number of clusters, GEE models estimation will be followed by t test with the Kauermann and Carrol-corrected sandwich estimator. In alternative, we will use the Wald t test with the FG-corrected sandwich estimator, depending on the variation in cluster size (function saws from R package saws) [50]. FG-corrected sandwich estimation is not possible with mixed models. For this reason, we will apply GEE models for the analyses. BMI z-score and other secondary outcomes at baseline will be used as covariates to adjust the models. Final models will be adjusted for baseline covariates such as: age, sex, mothers educational level, adherence to the Mediterranean diet, PA, and the corresponding anthropometric variable (function mgee from R-packagesaws). A fidelity score will also be included as a covariate in the models. Differences between the intervention and control group were considered significant if *p*<0.05. All analyses will be carried out using SPSS V21.0 and R.

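### The 80% power stated for each edition makes no allowance for centre clustering and is aimed at a different analysis from the pooled, cluster-corrected one that is planned

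*Protocol article*

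**What the plan says.** All references are to the protocol article.

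- **Size and scope (section on sample size).** The requirement is given edition by edition: "We estimate that it will be necessary to include 270 children and their parents, both in the intervention and control groups, per edition". The target is a zBMI fall that is larger by 0.15 in the intervention arm than among controls, and it is expected to reach significance. The next sentence fragment ties this to single editions: "From the PRE to POST evaluations, for each of the three editions".
- **Inputs (same section).** "We assume a 0.05 alpha risk, a 0.2 beta risk in a bilateral contrast, and 20% loss to follow-up". A general online calculator was used. No SD, ICC or design effect is given.
- **Dependence (same section).** Families with two eligible children are expected to be clearly fewer than families with one, and from this the article concludes: "Therefore, we performed a simplified approximation of the sample size by counting only for one outcome (zBMI of one child".
- **Structure (Subjects).** "A total of 30 CCC (15 in the intervention group and 15 as controls) will be involved per edition". Each centre contributes 18 children, and at least one adult and one child enrol per family. On totals, "we expect a total participation of 540 children and 400 adults per edition".
- **Analysis (Statistics).** "We will analyze the pooled data from the three timely different editions with a 10-month intervention each". Allocation is by centre. GEE models with a small-sample corrected sandwich estimator are planned because there are few clusters, with adjustment for baseline zBMI and other covariates. The Evaluation plan also describes the final evaluation as one of pooled data.

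**The concern.** The analysis section recognises that children within a centre are correlated and that there are few centres. The sample size section shows no allowance for either. Children in one centre share educators, neighbourhood and workshop delivery, so some positive correlation is plausible. Any positive correlation makes 270 children worth fewer than 270 independent ones.

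The power statement also refers to a single edition, while the stated inference is pooled over three. As written, the article gives a power figure for a comparison that is not its main analysis, and none for the one that is. A reader who takes the 80% at face value could give a single edition's result more weight than it can bear.

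**Working it through.** **Inputs from the article:** difference 0.15; alpha 0.05 two-sided; power 80%; loss 20%; 270 children per arm per edition; 15 centres per arm; 18 children per centre (15 × 18 = 270).

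**Inputs that are assumptions:** SD (not stated, so back-solved), ICC (0.01 to 0.05 shown) and sibling correlation (0.4, for illustration).

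**Step 1. What 270 implies.** The figure cannot be reproduced independently without an SD. Evaluable children per arm: 270 × 0.8 = 216. With no design effect, n = 2 × SD² × (1.960 + 0.842)² / 0.15². Setting n = 216 gives

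SD = √[216 × 0.15² / (2 × 2.802²)] = 0.556.

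With that SD, 216 per arm gives exactly 80% under the normal approximation, so no reserve is visible. If loss was instead applied as n × 1.2, the implied SD is 0.568. If it was not applied at all, it is 0.622.

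**Step 2. Centre clustering, one edition.** Analysed children per centre: 18 × 0.8 = 14.4. Design effect DE = 1 + (14.4 − 1) × ICC, effective n = 216/DE, and the standard error of the difference is SD × √(2/effective n). Power is from a noncentral t with 30 − 2 = 28 degrees of freedom, to reflect 30 centres.

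| ICC | DE | Effective n per arm | Power, SD 0.556 | Power, SD 0.50 | Power, SD 0.45 |
|---|---|---|---|---|---|
| 0 | 1.00 | 216 | 77% | 85% | 92% |
| 0.01 | 1.13 | 190 | 72% | 81% | 88% |
| 0.02 | 1.27 | 170 | 67% | 76% | 84% |
| 0.05 | 1.67 | 129 | 55% | 64% | 73% |

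The drop from 80% to 77% at ICC 0 comes from the t reference alone. Under the normal approximation with SD 0.556, power is 75%, 70% and 58% at ICC 0.01, 0.02 and 0.05.

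**Step 3. Siblings (secondary).** Per arm and edition, 540/2 = 270 children and 400/2 = 200 adults. With at least one adult per family there are at most 200 families. If no family enrols more than two children, at least 270 − 200 = 70 families have two, leaving 130 with one. The family term is (70 × 4 + 130)/270 − 1 = 0.519, to be multiplied by the sibling correlation. At an assumed correlation of 0.4 and ICC 0.02, DE = 1.268 + 0.4 × 0.519 = 1.475, and power is about 61% (SD 0.556, 28 df). The 0.519 is computed on enrolled children. If children are lost independently it shrinks by a factor of 0.8, and power is about 62%.

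**Step 4. The planned pooled analysis.** Evaluable per arm: 3 × 216 = 648, in 45 centre-editions per arm. With the same SD and DE, and 58 degrees of freedom (60 distinct centres less 2), power for 0.15 is about 99%, 99% and 96% at ICC 0.01, 0.02 and 0.05. Under the normal approximation it stays at 80% until DE reaches 648/216 = 3, that is, ICC = 2/13.4 ≈ 0.15. These figures treat the 90 centre-editions as independent. That is approximate, because Table 1 has 30 of the 60 centres serving first as control and then as intervention.

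**The case against.** **The size of the shortfall cannot be established from the article.** This stands. The SD of 0.556 is obtained by assuming no design effect and exactly 80% power, so any positive ICC must then give less. A smaller SD, or the variance reduction from adjusting for baseline zBMI, could offset part or all of the loss: at SD 0.50 and ICC 0.01 power is still 81%. But the article claims no such margin, so the right statement is that the 80% is unsupported.

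**The planned inference is pooled and well powered.** This stands too. A reader might infer that the trial as a whole is underpowered. Step 4 does not support that for the planned effect of 0.15.

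**The sibling approximation is disclosed.** A reader might infer that the counts of 540 children and 400 adults contradict it. They do not. The sentence compares families, and 70 two-child families against 130 one-child families agrees with it. What remains is that 70 families among 200 is not negligible.

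**No edition-by-edition test is laid down.** A reader might multiply the per-edition powers to get the chance that all three editions succeed. The article sets no such criterion, and successive editions share centres, so that product answers a question the plan does not pose. The per-edition reading rests on a broken sentence, though it is the natural one, and the requirement of 270 per arm is itself stated per edition.

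**Conclusion.** The point holds in a limited form. The per-edition 80% is given without an SD, an ICC or any allowance for centre clustering, in a design that allocates 15 centres per arm and analyses them as clusters. If 270 is 216/0.8 with no design effect, per-edition power is about 72%, 67% and 55% at assumed ICCs of 0.01, 0.02 and 0.05, against 81%, 76% and 64% if the SD is 0.50. Siblings could lower it further, by an amount that depends on an unstated correlation.

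The power statement also targets the wrong analysis. The pooled contrast, which the article plans, is not undermined: about 96–99% for 0.15 over the same ICCs, subject to the independence approximation for centres that appear in both arms. This is a statement to correct in the text. It does not threaten the trial's main conclusion.

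**What to change.** In the Sample size calculation section:

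1. State the SD, whether it refers to zBMI itself, its change or the baseline-adjusted residual, and where it comes from.
2. State an ICC range for centres and apply DE = 1 + (m − 1) × ICC with m = 14.4 analysed children per centre.
3. Restate power for the pooled three-edition zBMI contrast, noting that 30 centres contribute to both arms in successive editions.
4. Add a sensitivity allowance for siblings, based on the expected 270 children and at most 200 families per arm and edition.
5. Withdraw the 80% power and the expectation of significance for each edition.

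The cost is text only. No extra participants or centres are needed. Any per-edition power figure that is kept would probably be less favourable than 80%, unless the stated SD or the gain from baseline adjustment justifies it.

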### Intervention

The FIVALIN project is an FBI addressed to school age children (8- to 12-year-old) and their parents/caregivers. It has been created to be part of a Multi-Level Multi Component (MLMC) intervention that pretends to prevent childhood obesity from early ages, and along all the developmental stages, until adulthood. The pre-adolescence stage is a key period to sustain the healthy lifestyles promotion activities to prevent a deterioration at subsequent stages.

The FIVALIN project will be developed in three editions (1st 2019/2020; 2nd 2020/2021; 3rd - 2021/2022) of 10months each. The plan will be coordinated by the multidisciplinary health team of the GF, supported by educators of the CCC and a trained team of volunteers. We expect that the GF team will be stable. To ensure intervention consistency, we will activate different strategies (see Additionalfile1). Volunteers will be recruited by GF. They will contact the entity and, after a welcoming training, they will be involved in the project activities.

The study will be conducted after school time in CCC in the metropolitan area of Barcelona. In CCC, parents are encouraged to be part of their childrens education. For the intervention group, we define two modalities of participation (low and high), depending on the project intensity. The main difference between the two modalities is that children participating in the high intensity modality will do an extra activity, attending 32 sports educational sessions implemented by CCC educators. Each CCC will choose the modality that best fits their internal organization (see Table2 and Figs.1, 2 and 3)*.* Additionally, educational material, mobile messages, and videos will be sent to families in order to reinforce the health behaviors promoted during the workshops and sport educational sessions. Moreover, mobile messages will remind workshops date and hour to promote the participants attendance. CCC participating in the control group will be invited to be part of the intervention group in the next edition. The control group will receive the usual care provided in the CCC program plus a pre-evaluation and post-evaluation session. Moreover, they will receive a family workshop aimed to generate healthy lifestyle awareness and engagement, in order to reduce shortcomings in the post-evaluation.

**Table 2 Tab2:** FIVALIN project activities description by participation options

Activity description	Intervention		Control
	High intensity	Low Intensity	
**CCC**			
**Email and phone calls** to invite CCC to participate in the project.	Yes	Yes	Yes
**Communication material delivered**: 1 poster per CCC and 1 project introduction leaflet to each participant family.	Yes	Yes	No
**1 qualitative session implemented** with CCC educators (2h) before the project starts in the CCC to know participants family sociodemographic characteristics, their healthy lifestyles, and the CCC particularities.	Yes	Yes	No
**3 training (4h/training)**: face to face training with all the CCC participants educators every 2 months in the GF headquarter to promote the FIVALIN community, and share project methodology, theoretical basis, and project follow-up indicators.	Yes	Yes	No
**Sport educational sessions guide delivered to CCC**. The guide contains all the sport educational sessions that should be implemented by the CCC educators. For each healthy habit, the guide includes: i) Health messages definition; and ii) Sport educational sessions description: 8 sport educational sessions for health topic.	Yes	No	No
**Sport material box delivered to CCC** with all material needed to implement the sport educational sessions.	Yes	No	No
**Follow-up online meetings** (1h/meeting) with CCC educators.	Yes. 6 meetings	Yes. 3 meetings	No
**Children**			
**32 sport educational sessions** (1h/session) implemented by CCC educators using the sport educational sessions guide and sport material delivered. For each healthy habit, 4 health messages are promoted. For each healthy habit, 2 sport educational sessions are implemented.	Yes	No	No
**Family (children and adults)**			
**8 family workshops** (2h/workshop) involving a group of 15 to 20 children and parents from each CCC implemented in the CCC by GF staff with the support of CCC educators.	Yes. 8 Workshops: (1) Baseline evaluation (2) Welcoming (3) Sleep duration and quality (4) Healthy Diet (5) Emotional Wellbeing (6) PA & Sport (7) Closing (8) Final evaluation		Yes. 3 Workshops: (1) Baseline evaluative (2) General health awareness (3) Final evaluation
**32 mobile messaging** sent to participants families by using text, images, and infographics methods: (1) 8 mobiles messages, 1 before each family workshop, to recall families and promote their attendance. (2) 8 mobile messages, 1 after each family workshop, to reinforce the health topics promoted in the workshops. (3) 16 mobile messages, 1 after each cycle of 2 sport educational sessions dedicated to each healthy habit to reinforce it.	Yes	Yes	No
**8 challenges videos** done by high profile supporters (such as professional athletes and celebrities) posing a healthy challenge as a family related to one health topic.	Yes	Yes	No
**Health promotion educational material** shared with families after each workshop to reinforce the health messages shared in the sessions and workshops.	Yes	Yes	Yes

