**Fig. 7 Fig7:**
[figure not shown]
FIVALIN causal pathway

The following strategies will be applied to promote adherence and prevent attrition during the project planification and implementation: i) carry out a qualitative session in each participant CCC and community before starting the intervention; ii) facilitate the logistics for attending the workshops by choosing CCC located in the families own communities and providing a childcare service for children under 5years; iii) implement participative and respectful activities during the family workshops, to highlight each positive lifestyle behavior, independently of the cultural background, helping to generates a positive family attachment; iv) deploy a process evaluation protocol to identify areas for improvement, considering families, educators, and CCC opinions; v) consider various individual strategies based on the Motivational Interviewing principles directly addressed to parents (making individual follow up calls, using incentives, sending mobile messages to recall and thanks their participation in the project family workshops).

In conclusion, the plan consists of a multicomponent intervention with strategies at different levels (childrens education, families, and centers organization), that include several activities.

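### As Table 2 is written, attendance reminders for the evaluation sessions go to intervention families only, which may produce unequal loss to follow-up; the attrition strategies listed in the text do not agree with it

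*Protocol article*

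**What the plan says.** Table 2 (Family rows) lists eight workshops for the intervention arm. The first is the baseline evaluation and the list ends with "7) Closing (8) Final evaluation". The control arm has three: "1) Baseline evaluative (2) General health awareness (3) Final evaluation". In both arms, then, the first and last workshops are the outcome assessments.

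The mobile-messaging row of the same table describes 32 messages of three kinds. One kind is "8 mobiles messages, 1 before each family workshop, to recall families and promote their attendance". The row is marked Yes for high intensity, Yes for low intensity and No for control.

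The running text of the Intervention section says that "mobile messages will remind workshops date and hour to promote the participants attendance". This stands among the components sent to intervention families, before the control condition is described. Control families are to receive usual care, the two evaluation sessions and "a family workshop aimed to generate healthy lifestyle awareness and engagement, in order to reduce shortcomings in the post-evaluation".

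After Fig. 7, the same section lists strategies to promote adherence and prevent attrition. They include "making individual follow up calls, using incentives, sending mobile messages to recall and thanks their participation in the project family workshops". That list names no arm.

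The Sample size calculation allows for "20% loss to follow-up" as one figure, with no rate by arm. The Statistics section plans GEE models adjusted for baseline zBMI and other baseline covariates.

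**The concern.** A reminder to attend the session at which the outcome is measured is part of collecting data. It is not part of the treatment under test. If it is bundled with the intervention and withheld from controls, the chance of having a final zBMI may depend on arm for a reason unrelated to the intervention's effect. Allocation here is by convenience, so the comparison already leans on adjustment, and an avoidable arm-dependent step in outcome collection adds a further possible source of bias.

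The protocol itself treats reminders as a way to raise attendance. Its Discussion links low participation to low SES, stress, single parenthood and difficult living circumstances. Families who miss the final evaluation may therefore differ from those who come. What is at stake is bias in the zBMI contrast; power is affected little.

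**Working it through.** **1. Does the reminder reach the evaluations?** Eight reminders, one before each workshop, are set against eight intervention workshops. Workshops 1 and 8 are evaluations, so both are covered. Control workshops 1 and 3 are the same evaluations, and Table 2 gives no message for them.

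**2. Which of the two reminders matters for loss?** The baseline reminder affects who is measured at entry. Only the final-evaluation reminder bears on loss to follow-up.

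**3. Do the passages agree?** The attrition list in the text names recall messages and calls for the project workshops without limiting them to an arm, while Table 2 says No for control messaging. The list does not clearly override the table. Its first item, a qualitative session in every participating centre, is also marked No for control in Table 2. Either the list describes intervention centres only, or it conflicts with the table more than once.

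**4. The plan's own figure.** 270 per group per edition, with alpha 0.05 two-sided, power 80%, difference 0.15 and 20% loss. No SD is stated, so 270 cannot be reproduced independently. Back-solving: 270 × 0.8 = 216 evaluable per group, and SD = 0.15 × √(216/2) / (1.960 + 0.842) = 0.556. If loss was instead allowed for by multiplying by 1.2, then 270/1.2 = 225 and SD = 0.568.

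**5. Power.** At SD 0.556, with loss given as intervention/control: 80.1% at 20%/20%, 79.9% at 15%/25% and 77.3% at 20%/30%. Power moves little unless total loss rises.

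**6. Bias, illustration only.** Let d_I and d_C be the loss in each arm, and g the mean zBMI change in lost children minus that in retained children, taken as equal in both arms. The retained mean in an arm differs from that arm's full mean by −d × g. The completers' contrast (intervention minus control) is therefore shifted by (d_C − d_I) × g.

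| Loss, intervention/control (assumed) | g = 0.1 | g = 0.2 | g = 0.3 | g = 0.5 |
|---|---|---|---|---|
| 20%/20% | 0 | 0 | 0 | 0 |
| 15%/25% or 20%/30% | 0.01 | 0.02 | 0.03 | 0.05 |
| as % of 0.15 | 7% | 13% | 20% | 33% |

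The sign reverses if the intervention arm loses more, or if lost children do better than retained ones. With more control loss and g positive, the shift works against the intervention: a true −0.15 would appear as −0.13 at a shift of 0.02.

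**7. What a small bias does to the pooled test.** 3 × 216 = 648 evaluable per arm. Ignoring clustering, SE = 0.556 × √(2/648) = 0.031. With no true effect, a bias of 0.02 raises the two-sided rejection rate from 5% to about 10%, and 0.03 raises it to about 16%. Clustering would normally enlarge the SE and soften this.

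**The case against.** A reader might infer that loss to follow-up will differ by arm and that controls will lose more. The documents do not support that. No loss rate by arm is given, and several measures do reach controls. The Evaluation plan gives families in both groups an incentive after assessment. Controls have an awareness workshop. For centres, "CCC participating in the control group will be invited to be part of the intervention group in the next edition". Intervention families also face eight workshops against three, which could raise loss in that arm, and the reminders might offset it. All of this stands.

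The table cell may also be coarse. Low intensity is marked Yes for the whole messaging row, although 16 of the 32 messages follow sport sessions that it does not have. So No for control might mean only that controls do not get the full package. That is fair, but it leaves an ambiguity to be resolved, since the Intervention text also places reminders within the intervention package.

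The illustration rests on invented loss rates and gaps. It also ignores the planned adjustment for baseline zBMI, age, sex, mother's education, diet and physical activity. Bias remains only if lost children differ in zBMI change after that adjustment. Low SES is an inclusion criterion, so it separates lost from retained children poorly. These limits stand too, and the figures show scale only.

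Two further inferences fail. The single 20% loss figure does not assert equal loss by arm, so the contact plan does not contradict it. The leaflet marked No for control in Table 2 need not be the recruitment material described under Subjects, and it has no bearing on loss at the final evaluation.

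**Conclusion.** The point holds as a cheap improvement and a reconciliation. As written, Table 2 ties evaluation-session reminders to the intervention arm, and the attrition list in the text does not fit cleanly with it. Confidence is high on that asymmetry and limited on its effect.

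Unequal loss is a risk that the documents neither quantify nor establish. If it occurs, it could bias the zBMI comparison in either direction by an unknown amount. The range of 0.01 to 0.05 assumes a 10-point difference in loss, a gap of 0.1 to 0.5 in zBMI change between lost and retained children that is the same in both arms, and no baseline adjustment. None of these values comes from the protocol. If control families are in fact reminded of their evaluations in the same way, correcting Table 2 settles the main issue.

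**What to change.** 1. Define reminders for the baseline and final evaluations, and calls to families who do not attend them, as data-collection procedures. Send them in both arms with the same content, timing and number of attempts.
2. Keep health-topic messages and reminders for the content workshops as intervention only.
3. Amend the messaging row of Table 2 so that evaluation reminders have their own line, and state in the attrition list which arm each measure covers.
4. Report attendance at the final evaluation, and loss, by arm and edition.

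The cost is one or two extra texts, and possibly a call, per control family, with no health content. The Evaluation plan wants the same methodology in all three editions because the data are pooled. Any change made between editions must therefore be dated and documented, so that loss can be read edition by edition.
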